## Abstract

**Background:**

Cancer is one of the major health issues worldwide. An increasing number of cancer patients are offered treatment with surgery, chemotherapy and radiotherapy. Traditional Chinese medicine (TCM) is one of the most common complementary therapies offered to cancer patients in Taiwan. We designed a randomized, double-blind, placebo-controlled clinical trial to evaluate the efficacy of TCM in patients with cancer.

**Methods/design:**

In this study, inclusion criteria are postoperative patients with histologically confirmed cancer within 3 years who are undergoing chemotherapy or radiotherapy, more than 18 years old, have given signed informed consent, have the ability to read Chinese, and the ability for oral intake.

Exclusion criteria include being pregnant, breast feeding, having completed chemotherapy or radiotherapy, brain metastasis with Eastern Cooperative Oncology Group (ECOG) performance status of two to four, delusion or hallucinations, acute infection, and have received medications under other clinical trials.

The patients were separated into an intervention group (Shen-Mai-San, SMS) and a placebo group for four weeks using a randomized, double-blind procedure. The European Organization for Research and Treatment of Cancer (EORTC) Quality of Life questionnaire (QOL-C30) was used to evaluate the quality of life. General data, hemoglobin (Hb), hematocrit (Hct), glutamic-oxalacetic transaminase (GOT), glutamic-pyruvic transaminase (GPT), blood urea nitrogen (BUN), creatinine, carcinoembryonic antigen (CEA), TCM diagnosis data and heart rate variability (HRV) were also recorded. These data were collected at baseline, two weeks and four weeks after receiving medication. The patients were prescribed granules which contained therapeutic medicines or placebo. Paired-T test was used for statistical analysis.

**Discussion:**

Shen-Mai-San is composed of processed *Ginseng radis, Liriope spicata, and Schizandrae fructus*. It was found to be effective for treating cancer-related fatigue and had anti-fatigue activity. In TCM theory, SMS has a synergistic effect for qi and yin deficiency and has the ability to prevent fatigue. The symptoms of qi and yin deficiency are similar to chemotherapy- or radiotherapy-induced side effects. In order to evaluate the efficacy of SMS on cancer treatment, we designed a randomized, double-blind, placebo-controlled trial.

**Trial registration:**

This study is registered to Clinical Trails.gov NCT01580358

## Background

Cancer has been the most horrible disease worldwide. In Taiwan, cancer has been ranked as the leading cause of death since 1982 [1]. Liver cancer, lung cancer and colon cancer are the leading cancers and account for 50% of all cancers in Taiwan [1]. The treatment of cancer includes surgery, chemotherapy, radiotherapy, target therapy, and so on. The choice of management depends on cancer type and stage. Treatment generally has a beneficial effect on curbing the progression of the disease, but sometimes causes disturbing side effects, such as nausea, vomiting [2], mucositis [3], general weakness [4] and so on which may decrease a patient’s quality of life [5]. The use of complementary and alternative medicine (CAM) has increased over the past years around the world [6]. Some studies indicate that the use of CAM is found more frequently in patients with cancer than in the general population and the use of CAM is common in these patients [7,8]. The use of CAM increased among these patients who had a lower quality of life [9]. Many studies indicate an improvement in the quality of life and general health in cancer patients adopting CAM treatment [10,11]. CAM treatment includes dietary supplements, prayers, traditional Chinese herbs and botanicals [12].

Traditional Chinese medicine (TCM) is one of the most common CAM used in Taiwan. Some cancer patients search for a second opinion or TCM instead of regular treatment. Many patients in Taiwan turn to TCM due to poor quality of life or general weakness after surgery, radiotherapy or chemotherapy. Some studies reported that TCM did demonstrate some beneficial effects on maintaining immune function and liver protection in patients who were simultaneously receiving chemotherapy [13,14]. The purpose of this study is to evaluate the efficacy of TCM in improving the quality of life of cancer patients undergoing chemotherapy or radiotherapy. Although many CAMs have demonstrated positive effects on lessening the side effects suffered after chemotherapy or radiotherapy, a rigid validation using a randomized controlled trial (RCT) remains the best way to examine the effect of TCM in these patients.

## Methods/Design

### Design

The study is conducted as a randomized, double-blind, placebo controlled trial to examine the effects of TCM in patients with cancer who are undergoing chemotherapy or radiotherapy. All participants are randomly assigned to an intervention or placebo group. The study procedures and informed consent form have been approved by the Institutional Review Board of Changhua Christian Hospital in Taiwan. (IRB no.070301). Figure 1 illustrates the flow diagram of the trial for both the intervention and placebo groups.

**Figure 1 F1:**
[figure not shown]
TCM therapeutic efficacy trial flow chart.

### Medication

According to the guidelines for clinical trials of new Chinese medicine announced by the Department of Health, Executive Yuan in Taiwan [15], only formulae recorded in ancient TCM books may be used for clinical trials in Taiwan. The formula employed in this trial, Shen-Mai-San (SMS) has a long history of application to disease treatment in China starting in the 12th century [16]. SMS is composed of three herb ingredients, namely *Ginseng radis*, *Liriope spicata*, and *Schizandrae fructus*. It was initially used for the treatment of a dual deficiency of qi and yin with symptoms of thirst and general weakness while suffering from heat stroke, fatigue, and so on [17]. According to TCM theory, SMS can reduce fatigue, thirst, general weakness, and so on. SMS is widely used now to treat patients with cardiac disease, fatigue and cancer [18,19]. Many patients have symptoms of general weakness, thirst, and fatigue after chemotherapy or radiotherapy. These symptoms are similar to the syndrome of qi and yin deficiency in TCM theory. In order to evaluate the efficacy of SMS in cancer patients after chemotherapy and radiotherapy, a randomized, double-blind, placebo-controlled trial will be performed.

SMS is manufactured as a concentrated herbal extract, packed 0.5 g per capsule, and labeled by Sun-Ten, a pharmaceutical company in Taiwan with good manufacturing practice (GMP). The placebo capsules are prepared with 0.5 g starch inside the same colored and sized capsules.

### Participants

Patients will be recruited from the outpatients of the Oncology and Chinese Medicine Department in ChangHua Christian Hospital, a medical center in central Taiwan. Sixty patients will be recruited for the study and divided into an intervention group and a placebo group.

### Inclusion criteria

In this study, inclusion criteria are as follows: (1) postoperative patients with histologically confirmed cancer within 3 years who are undergoing chemotherapy or radiotherapy; (2) more than 18 years old; (3) signed informed consent; (4) able to read Chinese; and (4) have the ability to take medicine by mouth.

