### Exclusion criteria

Exclusion criteria include: (1) being pregnant; (2) breast feeding; (3) had completed chemotherapy or radiotherapy; (4) brain metastasis with Eastern Cooperative Oncology Group (ECOG) performance status of two to four; (5) suffering from delusion or hallucination; (6) acute infection; and (7) had received medications for other clinical trials.

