### Intervention

One experienced TCM physician will be assigned to record the general data, TCM diagnostic data and prescribed medication for two weeks at the first visit. The patients will take the prescription to the pharmacy and the CRC will give either SMS or placebo in a capsule containing either 0.5 mg medication or starch. Patients will take eight capsules three times a day. The intervention period will be four weeks. Two weeks and four weeks after the first visit, patients will come back to out-patient-department (OPD) for clinical evaluation and medication.

After four weeks on the prescribed medication, the patients will stop taking SMS and placebo for another four weeks and then come back to OPD for clinical evaluation.

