### Primary outcome

Quality of life is evaluated multi-dimensionally using the Taiwan Chinese Version of the EORTC Quality of Life Questionnaire C30 (QLQ-C30). The patients will complete the questionnaire at baseline (first visit), two weeks later (second visit), four weeks later (third visit) and eight weeks later (fourth visit). The score will be calculated and compared within group and between groups before and after medication.

The laboratory data collected will be also used to evaluate the general health status and monitor the liver and renal functions to assess the safety of SMS.

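### Cancer treatment may end during the four study weeks, so within-arm QLQ-C30 change cannot show an SMS effect; efficacy should rest on the between-arm comparison

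*Protocol article*

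**What the plan says.** The Background gives the aim as "improving the quality of life of cancer patients undergoing chemotherapy or radiotherapy". Under Inclusion criteria, item 1 admits "postoperative patients with histologically confirmed cancer within 3 years who are undergoing chemotherapy or radiotherapy". Under Exclusion criteria, item 3 removes patients who "had completed chemotherapy or radiotherapy". Both conditions apply at entry. Neither names a phase of the course or a minimum amount of treatment still to come.

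Under Intervention, "The intervention period will be four weeks", and return visits are timed from the first visit. Under Primary outcome, the QLQ-C30 is completed at baseline and at weeks 2, 4 and 8, and "The score will be calculated and compared within group and between groups before and after medication". Statistical analysis names one test, the paired t-test.

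The Medication section describes the population differently: "In order to evaluate the efficacy of SMS in cancer patients after chemotherapy and radiotherapy".

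**The concern.** A patient in the last week of radiotherapy, or at the last chemotherapy cycle, meets the entry criteria and would spend most of the study medication period off cancer treatment. A patient who enters at the first cycle would spend the same four weeks accumulating toxicity. Both processes move quality of life whatever capsule is taken.

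A before-after change within the SMS arm adds these movements to any SMS effect and cannot separate them. If the paired t-test is read as evidence of efficacy, SMS could be credited with recovery or charged with toxicity. The between-arm comparison does not share that problem, but its result applies to a mixture of patients still on treatment and patients who have just finished.

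The wording adds to the uncertainty about the target population. *After* in Medication does not match *undergoing* in Background, Design and Inclusion criteria. Taken literally, exclusion 3 also removes a patient who has finished radiotherapy and is now on chemotherapy, although inclusion 1 admits that patient.

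**Working it through.** **Inputs from the article:** 60 patients in total, four weeks of study medication, visits at weeks 2, 4 and 8, and a paired t-test. The article gives no course lengths, no share finishing, no SD and no derivation of the 60, so there is no planned figure to reproduce. Everything marked *assumed* below is illustrative.

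**1. How many might finish within four weeks.** Assume entry is uniform over a course of L weeks, so the remaining course U is uniform on (0, L).
- Share finishing within the window: P(U < 4) = 4/L.
- Mean on-treatment share of the window: (8/L + 4(L − 4)/L)/4 = 1 − 2/L, so the off-treatment share is 2/L.

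| L (assumed) | Finish within 4 weeks | Window time off treatment |
|---|---|---|
| 6 weeks | 4/6 = 67% | 2/6 = 33% |
| 12 weeks | 4/12 = 33% | 2/12 = 17% |
| 24 weeks | 4/24 = 17% | 2/24 = 8% |

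**2. Within-arm comparison.** If 30% finish and recover 15 points on the 0–100 scale (both assumed), each arm shows a mean gain of 0.3 × 15 = 4.5 points that owes nothing to SMS.

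Twenty thousand trials were simulated with no SMS effect, 30 per arm and two-sided 5% tests. A share f of patients recovers by r SDs of change. Percentage of trials with a significant result:

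| f | Paired test in SMS arm, r = 0.5 | Paired test in SMS arm, r = 1.0 | Between-arm test, both r |
|---|---|---|---|
| 0 | 5% | 5% | 4.8–5.1% |
| 0.2 | 8% | 16% | 4.8–5.2% |
| 0.4 | 18% | 48% | 4.8–5.0% |
| 0.6 | 34% | 81% | 5.0–5.2% |

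The values of f cover most of the 17–67% range in step 1.

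**3. Between-arm comparison: added variance.** With the same 30% and 15 points, the variance added to the change score is 0.3 × 0.7 × 15² = 47.
- SD 20 (assumed): the standard error goes from 20 × √(2/30) = 5.2 to √447 × √(2/30) = 5.5, about 6% more.
- SD 25 (assumed): it goes from 25 × √(2/30) = 6.5 to √672 × √(2/30) = 6.7, about 4% more.

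Chance imbalance in the share finishing moves the arm difference with an SD of √(2 × 0.3 × 0.7/30) × 15 = 0.118 × 15 = 1.8 points. This is the same added variance expressed another way, and an ordinary two-sample test already allows for it.

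**4. Between-arm comparison: possible dilution.** With 30 per arm, 80% power at two-sided 5% needs a standardised effect of (1.96 + 0.84) × √(2/30) = 0.72. If SMS did nothing in patients who finish in the window (worst case), the effect becomes 0.72 × (1 − f), and power falls from 80% to 61%, 39% and 20% for f = 0.2, 0.4 and 0.6.

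**The case against.** A reader might infer that the trial does not measure benefit in patients undergoing treatment. The article does not support that. Every patient must be on chemotherapy or radiotherapy at entry, those who have completed it are excluded, and the share who then finish within four weeks is unknown. Following patients for a fixed time after randomisation, whatever happens to background therapy, is a legitimate choice, and the Discussion places side effects both during and after treatment.

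The article also plans a between-group comparison in a randomised, double-blind, placebo-controlled design. Recovery is balanced in expectation there, and the simulated error rate confirms it. This stands, and it limits the harm to the within-arm reading.

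The sizes are soft. Under uniform entry, patients who finish in the window have been off treatment for only two weeks on average at week 4, so 15 points of recovery for all of them is generous. Dilution requires that SMS has no effect once treatment ends, which nothing in the article says.

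The within-arm weakness would remain under any eligibility rule, because toxicity also accumulates in patients who stay on treatment. That is a reason to correct the analysis rather than the entry criteria.

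The article condenses a fuller protocol and its flow chart is not shown, so cycle-level scheduling or covariates may be specified elsewhere. That does not settle the within-group comparison and single named test, which the article states. *After* may mean between administrations, and exclusion 3 may be meant as having no ongoing treatment. Both are wording points, but the text leaves them open.

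**Conclusion.** The point holds in a limited form. Entry requires ongoing treatment but no minimum remaining course, and the visit clock is independent of the course, so some patients may finish during the study medication period.

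The within-group before-after comparison by paired t-test therefore confounds any SMS effect with recovery or accumulating toxicity. Under the assumed scenarios with f from 0.2 to 0.6, its false-positive rate in the SMS arm runs from 8% to 81% instead of 5%.

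The between-arm comparison is not biased by recovery. Its cost is a mixed population, a standard error about 4% to 6% larger in the worked example, and dilution of unknown size. These figures rest on assumed course lengths, share finishing, recovery, SD and 30 patients per arm.

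**What to change.** 1. State that the efficacy conclusion rests only on the between-arm comparison of week-4 QLQ-C30, adjusted for the baseline score. Report within-arm change descriptively.
2. For all patients, including the 36 recruited at manuscript submission, take from the chart the end date of chemotherapy or radiotherapy as planned at baseline. Before unblinding, name *treatment planned at baseline to run through week 4 (yes/no)* as an adjustment factor. Using the plan at baseline, not the actual end date, avoids adjusting for something that happens after randomisation.
3. Reconcile *after* in Medication with *undergoing* in Background, Design and Inclusion criteria. Reconcile exclusion 3 with inclusion 1 for patients who have finished one modality and are receiving the other.

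The cost is a little chart abstraction, one extra model term and a text correction. Changing eligibility is not recommended on this ground: with 36 of 60 recruited at submission, a new rule for the remaining 24 would create two entry populations in a small trial and would not repair the within-arm comparison.

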### Exclusion criteria

Exclusion criteria include: (1) being pregnant; (2) breast feeding; (3) had completed chemotherapy or radiotherapy; (4) brain metastasis with Eastern Cooperative Oncology Group (ECOG) performance status of two to four; (5) suffering from delusion or hallucination; (6) acute infection; and (7) had received medications for other clinical trials.

### Randomization

Patients who meet the inclusion criteria will be randomly assigned to an intervention group (SMS) or placebo group by the clinical research coordinator (CRC).

### Blinding

The patients will receive capsules either with SMS or placebo. These capsules are the same in appearance, color and shape. The researchers and patients will not know which group the patients are allocated to from the appearance of the medication given.

### Intervention

One experienced TCM physician will be assigned to record the general data, TCM diagnostic data and prescribed medication for two weeks at the first visit. The patients will take the prescription to the pharmacy and the CRC will give either SMS or placebo in a capsule containing either 0.5 mg medication or starch. Patients will take eight capsules three times a day. The intervention period will be four weeks. Two weeks and four weeks after the first visit, patients will come back to out-patient-department (OPD) for clinical evaluation and medication.

After four weeks on the prescribed medication, the patients will stop taking SMS and placebo for another four weeks and then come back to OPD for clinical evaluation.

### Data collection

We will collect basic data such as gender, age, cancer type, stage, and metastasis or no metastasis at base line. Other than the basic data, such as gender and age, laboratory data, for example, WBC, Hb, Hct, CEA, platelet and HRV will be collected. GOT, GPT, BUN, and creatinine will also be recorded to facilitate the evaluation of liver and renal functions.

### Statistical analysis

Statistical analysis will be performed by the Department of Mathematics and the Institute of Statistics and Information Science, National Changhua University of Education in Taiwan. We will use the statistical software R to analyze the data. Paired-T test will be derived for statistically analysis.

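### The only test named, the paired t-test, compares visits within one arm and does not fit the between-group comparison of SMS with placebo that the article plans

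*Protocol article*

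**What the plan says.** The article describes a parallel-group trial. The Design section states: "The study is conducted as a randomized, double-blind, placebo controlled trial to examine the effects of TCM in patients with cancer", and "All participants are randomly assigned to an intervention or placebo group". No matching of patients and no crossover is described. Under Participants: "Sixty patients will be recruited for the study and divided into an intervention group and a placebo group".

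The primary outcome is the EORTC QLQ-C30, completed at baseline and at two, four and eight weeks. For its analysis, the Primary outcome section says: "The score will be calculated and compared within group and between groups before and after medication".

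The Statistical analysis section names one procedure: "Paired-T test will be derived for statistically analysis". The Abstract says the same: "Paired-T test was used for statistical analysis". Neither place limits the paired test to the within-group comparison, and no test for independent groups is named anywhere in the article.

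**The concern.** A paired t-test needs two measurements that belong together, such as baseline and week 4 in the same patient. Patients in the SMS arm and patients in the placebo arm are different people, so the natural use of the test here is before against after inside one arm.

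That contrast does not isolate the effect of SMS. It also contains the placebo response, regression to the mean and the course of the patient's chemotherapy or radiotherapy. The last of these is not hypothetical: patients are under active treatment at entry, and the Discussion says that side effects of such treatment may lower quality of life. A change shared by both arms is therefore plausible, in either direction. A shared improvement could be credited to SMS; a shared decline could hide a real benefit. Finding the SMS arm significant and the placebo arm not significant is not a test of the difference between them either.

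At stake is whether the stated analysis matches the question that the placebo arm was included to answer.

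**Working it through.** **Matching test to comparison**

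| Comparison planned (Primary outcome) | Data structure (Design) | Test named (Statistical analysis, Abstract) | Fit |
|---|---|---|---|
| Within group | Same patient at two visits | Paired t-test | Yes |
| Between groups | Different patients, randomised, unmatched | Paired t-test, none other | No |

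**Size of the problem if efficacy were judged within arms**

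From the article: 60 patients in two groups. Assumed, because the article does not give them: equal allocation (n = 30 per arm), two-sided alpha 0.05, normally distributed change scores with the same SD in both arms, complete data, inert SMS, and a shared mean change of d SD of the change score. The article gives no value for d, so a range from 0 to 0.8 is shown. The article states no alpha, power or effect size behind the total of 60, so there is no planned figure to reproduce; the point does not depend on one.

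The paired t statistic in one arm follows a noncentral t distribution with df = n − 1 = 29 and noncentrality d × √30. The critical value is 2.045, and

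p(d) = P(|T| > 2.045).

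With d = 0.5, for example, the noncentrality is 0.5 × 5.477 = 2.739 and p = 0.754.

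The arms are independent, so the chance that SMS is significant and placebo is not is p(1 − p). At d = 0.5 this is 0.754 × 0.246 = 0.186.

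| Shared change d (SD) | SMS arm significant, p | SMS significant, placebo not, p(1 − p) |
|---|---|---|
| 0 | 5.0% | 4.8% |
| 0.2 | 18.5% | 15.1% |
| 0.3 | 35.5% | 22.9% |
| 0.4 | 56.3% | 24.6% |
| 0.5 | 75.4% | 18.6% |
| 0.8 | 98.9% | 1.1% |

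The second column rises steadily with d. The third peaks at 25%, where p = 0.5 (d about 0.37), and is small at both ends. At d = 0 it counts change in either direction; counting only improvement, it is 2.4%.

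**Check by simulation** (40,000 trials per scenario, same assumptions, d = 0, 0.2, 0.37, 0.5, 0.8). The paired test in the SMS arm was significant in 5.0%, 18.7%, 50.1%, 75.4% and 98.8% of trials, which agrees with the formula. A two-sample t-test on the change scores of the same simulated patients was significant in 4.8% to 5.1% across all five scenarios. The loss of error control therefore comes from the choice of comparison.

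**The case against.** The strongest objection is that the article does plan a comparison between groups. The paired test may be meant only for the within-group part, for which it is suitable, and a condensed article may leave the between-group model to a fuller document. Much of this stands. A reader might infer that the randomised comparison has no valid analysis at all, or that the value of the placebo arm is lost. The article does not support that: the between-group comparison is stated, and what is missing is a suitable named test for it.

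What remains is not mere silence. The article states a method twice, without restricting it, and that method does not fit half of the comparison it is meant to serve.

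A second objection also stands. Nowhere does the article say that SMS will be declared effective because its own arm changed, or because it changed significantly and placebo did not. A reader might infer such a rule from the single named test, but the error rates above hold only if that rule were used. They also depend strongly on an assumed shared change: with none, the within-arm test stays at 5%.

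One could also pair patients across arms arbitrarily and apply the named test. In the same simulation this kept the error at 4.9% to 5.2%. But the article gives no basis for such pairs, and the result would depend on how they were formed.

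**Conclusion.** The point holds in this form: the one test named in the Abstract and in the Statistical analysis section does not fit the between-group comparison planned under Primary outcome. This follows from the text alone and needs no assumption.

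The size is conditional. If efficacy were judged by the paired test in the SMS arm, the chance of a significant result with an inert product would run from 5% with no shared change to about 99% at 0.8 SD, under the assumptions of 30 per arm, two-sided 0.05 and equal change in both arms. A between-arm test holds about 5% over the same range.

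The correction should be made before analysis, because it concerns the trial's main efficacy question.

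**What to change.** In the Statistical analysis section and the Abstract, replace the paired t-test as the efficacy analysis with a between-arm comparison, for example:

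*Efficacy is assessed by the difference between SMS and placebo in [one named QLQ-C30 scale] at [one named visit], with patients analysed in the arm assigned, estimated by ANCOVA with baseline score and arm as terms and reported with a 95% CI. Within-arm paired results are descriptive and support no efficacy claim.*

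- **Scale and visit.** Both must be filled in. The instrument is described as multi-dimensional, so there is no single QLQ-C30 score to refer to, and the article does not rank weeks 2, 4 and 8. The end of the four-week treatment period is one candidate; the choice belongs to the trial team.
- **Model.** A two-sample t-test on change scores is the minimum valid correction. ANCOVA, or an equivalent mixed model over visits, is preferable for precision. With equal variances at both visits and baseline-to-follow-up correlation r, the ANCOVA variance is (1 − r²) / [2(1 − r)] = (1 + r)/2 of the change-score variance: 0.65, 0.75 and 0.85 at assumed r of 0.3, 0.5 and 0.7. This is a gain in efficiency and not part of the fault.
- **Further covariates.** These are optional, cost a few degrees of freedom, and should be limited to data shown to be collected. Metastasis is listed under Data collection; type of current treatment is not.

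The cost is a sentence or two in the analysis section, the matching line in the Abstract and a few lines of R. The core change needs no new patients or data.

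### A paired t-test is the only method named for a four-visit quality-of-life outcome that is also to be compared between groups; a repeated-measures model would use the collected scores and give that comparison

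*Protocol article*

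**What the plan says.** The Statistical analysis section gives the analysing department, the software and one test: "Paired-T test will be derived for statistically analysis". The Methods/design part of the abstract repeats it: "Paired-T test was used for statistical analysis". No other test or model appears in the article.

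The Primary outcome section places the QLQ-C30 at baseline and then "two weeks later (second visit), four weeks later (third visit) and eight weeks later (fourth visit". On the comparison it says: "The score will be calculated and compared within group and between groups before and after medication". The Intervention section makes week 4 the end of treatment and week 8 an off-treatment visit: "After four weeks on the prescribed medication, the patients will stop taking SMS and placebo for another four weeks". The Participants section sets the size: "Sixty patients will be recruited for the study and divided into an intervention group and a placebo group". The article states no alpha, power, effect size, SD, dropout rate or allocation ratio.

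**The concern.** The named method fits the described outcome poorly in two ways.

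- **It takes two time points at a time.** A paired difference exists only where both scores exist. A patient with baseline and week-2 scores but no week-4 score adds nothing to the baseline-to-week-4 comparison, and the week-2 score in hand cannot inform it. These patients are on chemotherapy or radiotherapy and are scored when they return to the outpatient department, so it is plausible, though not documented, that those who worsen miss later questionnaires.
- **It tests change within one group.** The Primary outcome section also plans a between-group comparison, which is the one that randomisation supports. Two separate paired tests, one per arm, do not make that comparison.

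At stake are a within-arm change that looks better than it is, possible bias in the arm difference, and some avoidable loss of precision.

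**Working it through.** **1. The plan's own figure.** The total of 60 cannot be reproduced, because no inputs are given for it. I assume 1:1 allocation (30 per arm), two-sided 5% and 80% power.

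**2. Assumptions for the illustration (none is in the article).** Score 0-100, SD 20, true change to week 4 of -5 in both arms. Correlation is 0.7 between adjacent visits and 0.5 between baseline and week 4. The log-odds of dropout after week 2 rise with decline from baseline to week 2.

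**3. How dropout carries over to the week-4 change.** Let D2 and D4 be the changes from baseline to weeks 2 and 4.

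- Var(D2) = 400 x (2 - 2 x 0.7) = 240
- Var(D4) = 400 x (2 - 2 x 0.5) = 400, so the SD of D4 is 20
- Cov(D2, D4) = 400 x (0.7 - 0.5 - 0.7 + 1) = 200
- Slope of D4 on D2 = 200 / 240 = 0.83

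So if retained patients are on average 1 point better than all patients on D2, the complete-pair week-4 change is 0.83 points too favourable.

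**4. Within-arm result (simulation; truth -5.0).**

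| Missing at week 4 | Complete-pair change | Range over slopes 0.05 to 0.15 log-odds per point | Estimate also using week 2 |
|---|---|---|---|
| 24% | about -2.4 | -2.8 to -0.9 | about -5.0 |
| 33% | about -1.4 | -2.1 to +0.5 | about -5.0 |

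Cross-check with step 3: the bias of 2.6 points at 24% needs retained patients to be 2.6 / 0.83 = 3.1 points better on D2. That is 3.1 / 15.5 = 0.2 of its SD (15.5 = square root of 240), a modest selection.

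**5. Between-arm result, with no true difference.**

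- Dropout random, or related to outcome equally in both arms: mean difference about 0 (at most 0.01 SD).
- Decline drives dropout in one arm only: about 2.7 points at 24% v 20% missing and about 3.6 at 33% v 30%.
- A second simulation, in which dropout occurred in one arm only and was related to the follow-up score, gave 0.03, 0.09 and 0.14 SD at base rates of 10%, 20% and 30%. With SD 20 that is 0.6 to 2.8 points.
- For scale, the standard error of the arm difference with 24 per arm is 20 x sqrt(2/24) = 5.8 points.

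**6. Precision.** Detectable differences come from two-sample t power.

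- 30 per arm: 0.74 SD. 24 per arm (20% lost): 0.83 SD.
- Squared partial correlation of week 2 with week 4 given baseline: (0.7 - 0.7 x 0.5)^2 / [(1 - 0.49)(1 - 0.25)] = 0.32.
- Relative variance: no loss 1/30 = 0.0333; complete cases 1/24 = 0.0417; using week 2 as well, 0.68/24 + 0.32/30 = 0.0390.
- Detectable difference with week 2 used: 0.736 x sqrt(0.0390/0.0333) = about 0.80 SD. About a third of the lost information comes back: (0.0417 - 0.0390) / (0.0417 - 0.0333) = 0.32.

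**7. If dropout depends on the unseen week-4 outcome.** At 24% missing and 0.05 log-odds per point of decline to week 4, complete pairs give about -0.9 and the model about -2.8, against a truth of -5.0. If dropout follows the week-4 level rather than the change, the gain can all but vanish.

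**8. Separate paired tests as a between-group comparison.** With no dropout, no arm difference, 30 per arm and the same change in both arms, exactly one arm was significant in 50% of runs (change 0.36 SD) and 37% (0.5 SD). A two-sample test on change stayed at about 5%.

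**The case against.** The strongest reply is that a test's name fixes neither the analysis set nor the handling of missing scores. Values can be imputed before a paired test. The article nowhere says that patients with incomplete questionnaires are excluded, and an article may leave missing-data rules to a fuller document. That stands: silence on missing data is not the point here. What remains is that a method is stated, twice, and it does not suit four visits and a between-group aim.

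A two-sample test on change, or ANCOVA on available week-4 scores, would lose the same patients. This is also true, but it only shows that other two-time-point methods share the weakness.

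A reader might infer that the result would describe completers only. It would not. Pairs are lost comparison by comparison, so a patient who misses week 8 still counts at weeks 2 and 4. A reader might also infer that the randomised comparison is broken. The documents do not support that, because it depends on how much dropout there is and whether its mechanism differs by arm, and neither is given. Even then, 2.7 points is under half the standard error of 5.8.

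Finally, the recovery of -5.0 in step 4 is partly built in, since dropout was generated from observed scores, as the model assumes. Step 7 shows the limit.

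**Conclusion.** The point holds in a limited form. The stated paired t-test, applied as written, uses only patients with both scores in each comparison, ignores the other visits, and does not supply the planned between-group comparison. That follows from the text alone.

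The sizes do not. Under the assumed SD, correlations and decline-related dropout, within-arm change is too favourable by about 2.6 points at 24% missing (5.0 - 2.4) and 3.6 at 33% (5.0 - 1.4). The arm difference is biased, by about 2.7 to 3.6 points, only where dropout relates to deterioration differently by arm. Most of the precision loss comes from absent data, and no choice of test removes it. The change is worth making because it is nearly free, not because the documents show that the result would be wrong.

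**What to change.** In the Statistical analysis section, and correspondingly in the abstract, replace the paired t-test for QLQ-C30 scores with a mixed model for repeated measures, fitted in R as already planned:

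- all randomised patients, in their assigned group;
- terms for arm, visit, arm-by-visit, baseline score and baseline-by-visit, with unstructured covariance;
- the between-arm difference at week 4 reported with its 95% CI;
- one delta-adjusted sensitivity analysis that penalises missing scores, with questionnaire completion shown by arm and visit.

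The cost is wording and code; no patients, visits or data are added. The Trial status section reports 36 of the planned 60 recruited at submission, so the change could be fixed before the final analysis.

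The downsides should be stated. The model assumes that missingness depends on observed scores. It removes only part of the bias if missingness depends on unseen ones, and it recovers only part of the lost precision. Patients with no score after baseline still add no outcome information, which is one reason for the sensitivity analysis.
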